#### 4.4.1.1. Description of Data Collection Methods

##### Data Collection via Tablet PC

##### **Collection and Analysis of Activity from Video Features on Tablet PC**

To estimate the activation of individuals during physical exercise and to infer the motivational status of persons with dementia based on this, movement analysis will be conducted using a video camera embedded in the Tablet PC. The Tablet PC should be placed upright on a table, with the camera directed towards the person performing the exercise.

At the start of each exercise session, a video with a 20-second recording duration will be captured by the webcam and stored in the data repository. Only the user's personal code will be saved with the video. The camera generates an output stream with 640x480 pixels at 30 frames per second (fps) or 2560x1920 pixels at 1 fps.

Upon return of the Tablet PC, the videos will be transferred by the JOANNEUM RESEARCH (JR) study team to a PC protected by a firewall at JR. An image analysis software, based on the method described by Cao et al. (2017), will extract and encode the skeleton data of the person in the video (see **Figure 2**). The video will then be deleted by automated software, ensuring that no JR staff member can view the appearance of the users. Only the skeleton data will be stored to extract kinetic energy and emotions following the methodology of Piano et al. (2014). Finally, only features such as emotion and energy for specific observation periods will be stored per anonymized user, while all other data will be deleted.

*According to the journal's guidelines, copyrighted images have been removed from the published version.*

(a)

(b)

*Figure 3 Exemplary Video Analysis of a User's Movements. The algorithm by Cao et al. (2017) enables the extraction of skeleton data from video images. Only the skeleton data is stored, associated with an anonymized code for the test person, while the video data is deleted immediately after analysis. The activation of the users is derived from the skeleton data.*

### **Analysis of Gaze Behavior on the Tablet PC**

To analyze gaze behavior, the study employs software designed to analyze webcam data on the Tablet PC. The video data is processed in real-time using a static eye-tracker on the Tablet PC. The video data itself is not stored; instead, after an initial calibration of gaze geometry, only metadata, such as fixations and saccades of the participants during tablet use, is automatically and continuously recorded. Training sessions for the antisaccade task and the "Visual Paired Comparison" test are prepared so that participants are unaware of the gaze behavior analysis. This approach ensures that participants focus on the task at hand while allowing the evaluation of executive functions (inhibitory functionality: Diamond et al., 2013).

Gaze Behavior Analysis Metrics:

#### **Antisaccade Task**

Participants view alternating blocks of prosaccade and antisaccade tasks on a 10.5" Tablet PC screen in a game-like format (24 trials per block, as per Kaufmann et al., 2010). Each trial presents a central stimulus for 2000 ms, followed by a peripheral star stimulus for 1000 ms on either the left or right side of the screen. Each trial in the antisaccade task is classified as follows:

- "No Error": When the participant's gaze does not fixate on the stimulus (i.e., the gaze is not within  $2^\circ$  of the line of sight directed at the stimulus at any measurement point).
- "Error": When the gaze line is within the threshold angle at least once during the trial.
- "Corrected Error": When the gaze line returns outside the threshold angle after an "Error" before the trial ends.
- "Uncorrected Error": When the gaze line does not return outside the threshold angle after an "Error" before the trial ends.

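### The antisaccade rule scores any trial without measured gaze near the star as No Error, so non-response, off-screen gaze and lost signal count the same as a correct antisaccade

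*Protocol*

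**What the plan says.** Section 4.4.1.1 of the protocol, under Antisaccade Task, describes blocks of 24 trials. Each trial shows a central stimulus for 2000 ms and then a star to the left or right for 1000 ms. The scoring is introduced with "Each trial in the antisaccade task is classified as follows", so it applies to all antisaccade trials. The classes are:

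- *No Error*: the participant's "gaze does not fixate on the stimulus". A 2-degree limit makes this concrete, and it is applied only to the gaze points that were measured.
- *Error*: a single hit suffices, the condition being "When the gaze line is within the threshold angle at least once during the trial".
- *Corrected Error*: the condition here is "When the gaze line returns outside the threshold angle after an" initial hit, within the same trial. No direction is named.
- *Uncorrected Error*: gaze stays in the zone until the trial is over.

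The preceding text, under Analysis of Gaze Behavior on the Tablet PC, gives the purpose: participants concentrate on the task "while allowing the evaluation of executive functions (inhibitory functionality"). The same text says that gaze is estimated from the tablet's webcam, that the video is not kept, and that only metadata such as fixations and saccades are recorded. Table 1 lists the task under executive functions and cognitive control.

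**The concern.** An antisaccade is a look away from a suddenly appearing target, to the opposite side. The rule tests only whether gaze came near the target. A participant who looks off the screen, does not respond, or is not seen by the webcam gets the same class as one who performed the task. No minimum of valid gaze samples is stated in the gaze sections or in section 4.5.

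This is not a detail left open for a later document. The protocol fixes the rule, and applying it as written misclassifies trials. In people with dementia using a tablet webcam, trials with no response or no usable signal are foreseeable.

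What is at stake is the meaning of the measure. Section 4.4.1.1 (Collection and Analysis of Cognitive Functions Using Tablet PC) plans to relate tablet performance to the psychological questionnaires to find correlates, and section 3 plans to feed collected data into a decision support system. A score that also reflects inattention and tracking quality would distort such correlations and any trend within a participant.

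**Working it through.** **Reading of the rule.** The section names both a central stimulus and a star, and does not say which one the 2-degree test refers to. The star is the only sensible reading: if the centre counted, nearly every trial would be an *Error*. On this reading *No Error* and *Error* are exact complements, so every trial falls into one or the other.

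**Step 1: apply the rule literally to gaze patterns.**

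| Gaze pattern in the trial | Class under the rule |
|---|---|
| Moves to the side opposite the star | No Error |
| Stays on the centre | No Error |
| Looks off the screen | No Error |
| Signal lost for the whole trial | No Error |
| Looks at the star, but signal is lost during that look | No Error |
| Looks at the star, then leaves it | Corrected Error |
| Looks at the star and stays | Uncorrected Error |

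Only the first pattern is an antisaccade, yet the first five share a class.

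**Step 2: effect on the score.** The protocol states no error rate, tracking rate or target for this task, so there is no figure to reproduce. Two quantities are assumed:

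- e: true error rate on trials with a response and a usable signal.
- q: share of trials with no response, off-screen gaze or no signal, all scored *No Error*.

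Observed error rate = (1 − q) × e + q × 0 = e(1 − q).

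| q | e = 0.30 | e = 0.50 | e = 0.70 | Errors per 24 trials at e = 0.50 |
|---|---|---|---|---|
| 0 | 0.30 | 0.50 | 0.70 | 12.0 |
| 0.10 | 0.27 | 0.45 | 0.63 | 10.8 |
| 0.20 | 0.24 | 0.40 | 0.56 | 9.6 |
| 0.40 | 0.18 | 0.30 | 0.42 | 7.2 |

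If those trials were left out of the denominator, the error rate would stay at e in every row.

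**Step 3: the opposite error.** One gaze point inside the zone is enough for an *Error*, so a noisy signal can create false errors. Let f be the chance of a false hit in a usable trial without a true error. Then:

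Observed error rate = (1 − q) × [e + (1 − e) × f].

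Setting this equal to e gives f = e × q / [(1 − q)(1 − e)]. With e = 0.50 and q = 0.20, f = 0.10 / 0.40 = 0.25. Below that false-hit rate the score understates errors; above it, the score overstates them. The net direction cannot be fixed from the protocol.

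**Step 4: where the measure is used.** Table 1 schedules the eye-tracking tasks within tablet training, every two weeks with the trainer, and not at T0 or T3. Section 4.3.1 gives that training to the intervention group; the control group receives the app licence only after the evaluation phase. Section 4.5 names the global score of the neuropsychological test battery (NTB) as the primary outcome and does not name gaze metrics.

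**The case against.** The strongest reply is that this is an exploratory tablet measure, and that the rule speaks of measurement points, which presupposes that gaze was measured. Software could drop untracked trials without the protocol saying so, and artefact handling is often specified elsewhere. That narrows the lost-signal case but does not remove it: the rule covers each trial and provides no class into which a dropped trial could go. Off-screen gaze and tracked non-response are unaffected by the argument.

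Holding the centre does withhold the reflexive glance at the star. For inhibition alone, *No Error* is defensible there. The fault in that pattern is only that a trial without an antisaccade is scored like one with it.

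Several stronger readings are tempting and are not supported:

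- *The flaw biases the trial towards a treatment benefit.* On the schedule in Table 1 there is no control-group series for this task, so there is no between-group estimate to bias. Section 4.5 does plan ANCOVA for other secondary outcomes but does not list gaze metrics among them.
- *The score will drift upwards as dementia progresses.* A rise in q from 0.10 to 0.30 at e = 0.50 would lift the *No Error* share from 55% to 65%, since 1 − 0.50 × 0.90 = 0.55 and 1 − 0.50 × 0.70 = 0.65. But the protocol gives no figure for q or its course, and false hits act in the opposite direction.
- *Lost tracking after an error counts as a correction.* The wording asks for the gaze line to be outside the zone; an absent signal does not meet that.
- *Nothing can be repaired later.* Saccades are stored, so their direction could be rescored. Lost signal is different: without video, it can be recognised only if validity was logged.

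**Conclusion.** The point holds as a defect in a stated scoring rule, of minor severity. Followed as written, the rule gives a correct antisaccade, no response, off-screen gaze and an absent signal the same class, and it accepts any departure from the star as a correction. That conclusion rests on the wording alone, with the star taken as the stimulus.

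The size is conditional. For assumed q between 0.10 and 0.40, misclassification alone lowers the observed error rate by 10% to 40% of its true value, before any offset from false hits. The affected results are trends within the intervention group and correlations with the psychological tests and questionnaires. The NTB primary outcome and the randomised comparison are not affected.

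**What to change.** In the Antisaccade Task text of section 4.4.1.1:

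1. State that the 2-degree zone refers to the star.
2. Score a trial as a correct antisaccade only when gaze moves to the side opposite the star.
3. Require movement to the opposite side for *Corrected Error* as well.
4. Add a separate class for no response or invalid signal, leave it out of the denominator, and report its share by session.
5. Log signal validity for each trial, because the video is not stored.

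The cost is a few lines of text and scoring code. Items 1 to 4 can largely be applied to the stored fixations and saccades; item 5 has to be in place while data are being collected. The downside is fewer scorable trials per 24-trial block, and so a less precise score in sessions with poor tracking.

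### Antisaccade trials are scored on single gaze samples, so the split between corrected and uncorrected errors mostly reflects tracker noise

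*Protocol*

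**What the plan says.** The Antisaccade Task text in Protocol section 4.4.1.1 sorts each trial into four labels by comparing gaze with a 2-degree zone around the star.

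An Error is scored "When the gaze line is within the threshold angle at least once during the trial". Its counterpart, No Error, is reserved for trials in which not one measurement falls inside that zone. The condition for upgrading to Corrected reads "When the gaze line returns outside the threshold angle after an 'Error' before the trial ends". The fourth label, Uncorrected, is left for trials where gaze, once inside, is never again measured outside.

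A central stimulus is "followed by a peripheral star stimulus for 1000 ms on either the left or right side of the screen", with 24 trials per block. The section on gaze behaviour says the study uses "software designed to analyze webcam data on the Tablet PC", calibrated once at the start. Video is not kept; only metadata such as fixations and saccades are recorded. The same section presents the task as a way to evaluate inhibition. Neither section states a gaze sampling rate, gaze accuracy, minimum dwell, filter or minimum number of valid samples.

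**The concern.** Each label turns on one measurement point. A single sample inside the zone is enough for an Error, and a single later sample outside it is enough for Corrected. Uncorrected therefore requires every sample after the first hit to stay within 2 degrees until the trial ends. A webcam estimate that jitters by a degree or so will rarely do that, even if the eye never leaves the star.

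Corrected also needs no movement to the opposite side, which is what would show that the participant had recovered the task. Jitter alone satisfies the definition. The Corrected and Uncorrected rates would then track noise and sample count rather than self-correction, and could differ between patients or sessions for reasons of lighting, posture or hardware. Because video is not stored, rescoring later may not be possible.

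**Working it through.** The Protocol states no error rate or tracker precision, so there is no figure to reproduce. The rule is applied literally.

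**Inputs from the Protocol:** 2-degree threshold, 1000 ms star, 24 trials per block, 10.5-inch screen.

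**Assumptions:**
- 30 samples per trial. The 30 frames per second figure is given only for the exercise video; the gaze rate is not stated.
- Independent Gaussian noise of SD s degrees on each axis, s from 0.5 to 5.
- Star 8 to 12 degrees from centre (a 10.5-inch 16:10 screen at 40 to 50 cm).
- The eye moves at 350 ms, leaving n = 19 samples, or at 600 ms, leaving n = 12.

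**A. Gaze goes to the star and stays there (a true uncorrected error).** The chance that one sample reads outside 2 degrees is q = exp(−2²/(2s²)). With n samples on the star:

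- P(Error) = 1 − qⁿ
- P(Uncorrected) = Σ qᵏ(1−q)ⁿ⁻ᵏ for k = 0 to n−1 (outside samples first, then all inside)
- P(labelled Corrected) = P(Error) − P(Uncorrected)

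| s | q | Corrected, n = 12 | Corrected, n = 19 |
|---|---|---|---|
| 0.5 | 0.0003 | 0.4% | 0.6% |
| 1 | 0.135 | 79.3% | 92.5% |
| 2 | 0.607 | 99.3% | 99.98% |

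Example at s = 1, n = 19: 1.000 − 0.0748 = 0.925. A simulation of 20,000 trials per setting that also includes the samples before the eye movement gives the same picture: under 1%, 79% to 93%, and over 99%. At s = 3 to 5 it detects an Error in 65% to 99% of these trials and labels 62% to 98% of all of them Corrected.

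**B. A correct antisaccade.** The star is at distance e from gaze before the movement and 2e after it. The per-sample hit chance at distance d is P(χ²₂ with noncentrality (d/s)² ≤ (2/s)²); call it a at d = e and b at d = 2e. Then P(false Error) = 1 − (1−a)³⁰⁻ⁿ(1−b)ⁿ. For the least favourable setting, e = 8 and n = 12:

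| s | a | b | False Error |
|---|---|---|---|
| 1 | about 0 | about 0 | about 0% |
| 2 | 0.00059 | about 0 | 1.1% |
| 3 | 0.00816 | about 0 | 13.7% |
| 4 | 0.01793 | 0.00006 | 27.9% |
| 5 | 0.02247 | 0.00056 | 34.0% |

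At e = 12 and n = 12 the last three rows fall to 0.3%, 3.0% and 8.3%. In the simulation, essentially all false Errors were labelled Corrected.

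**C. Sampling rate alone.** In the simulation at e = 10, s = 4 and a 350 ms movement, the false Error rate is 1.2% at 5 frames per second and 6.6% at 30. Per 24 trials that is 0.3 and 1.6.

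**D. Would three consecutive raw samples repair the rule?** The chance of a run of three inside samples, each with probability 1 − q, was computed for the sustained errors in A. Such a run occurs in over 99% at s = 1, in 36% (n = 12) to 53% (n = 19) at s = 2, and in 6% to 11% at s = 3. The existing rule detects over 99% at s = 2 and 93% to 99% at s = 3.

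**The case against.** The strongest reply is that the Protocol may intend scoring on fixations. It describes No Error as gaze that does not fixate on the stimulus, and the tracker records fixations and saccades, which normally means that samples have been grouped. That would remove single-sample strays. It carries some weight, but the text then spells out its own meaning as any measurement point, and the Error line says once is enough. At best the wording is ambiguous, and nothing states a minimum dwell.

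A reader might infer that noise turns a quarter to nearly half of correctly performed trials into Errors. A flat stray rate of 1% or 2% on every sample gives 1 − 0.99³⁰ = 26% and 1 − 0.98³⁰ = 45%. The documents do not support a flat rate unrelated to where the eye is looking. In the noise model the worst case is 34%, an average of 1.4% per sample (1 − 0.66^(1/30)), and it needs an SD of 5 degrees, the nearest star and a late movement.

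A reader might also infer that the trial's conclusions on cognition or inhibition are at risk. Protocol section 4.5 makes the global score of the neuropsychological test battery the primary outcome and does not name the gaze measures. The study is described as exploratory, and inhibition and executive function are also covered by the Go/Nogo component and the attention test battery. No 18-month antisaccade comparison is specified. The described use of the tablet data is to look for correlates with the questionnaires.

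**Conclusion.** The point holds as a minor scoring defect. As written, the Corrected and Uncorrected labels are not interpretable once gaze noise reaches about 1 degree per axis: 79% to 93% of sustained errors are then called Corrected, and over 99% at 2 degrees. At 0.5 degrees the problem all but disappears (under 1%). False Errors on correct trials are secondary, at about 1% or less up to SD 2, and become material only at SD 3 and above with unfavourable geometry.

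All these sizes rest on assumed noise, star position, movement time and 30 samples per trial, none of which the Protocol gives for the gaze task. That the label depends on single samples follows from the wording itself. The effect is confined to an exploratory tablet measure; no randomised comparison and no part of the primary outcome is shown to be affected.

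**What to change.** Apply the four categories to the fixations that the tracker already records, or to smoothed gaze, and not to raw samples. State the fixation definition or smoothing rule before data collection. Score an Error when a fixation falls within 2 degrees of the star. Score a Corrected Error only when a later fixation lands on the opposite side. State where an error followed only by a return to centre belongs. Report valid samples per trial alongside the rates.

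Do not substitute a run of three consecutive raw samples. Under the same assumptions it misses about half or more of sustained errors at SD 2 and about 90% at SD 3.

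The cost is a change to the scoring script and a few lines of Protocol text. Very brief glances at the star will no longer count. A sustained calibration offset is not removed by this change, because it shifts whole fixations.

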#### Visual Paired Comparison Task

In this task, a reference pattern and a comparison pattern are repeatedly presented to the participant, who must determine how the two patterns differ. The trial is terminated by the participant using a stop button upon reaching a decision. The following metrics are assessed according to Lagun et al., 2011:

- Novelty Preference (NP): The percentage of gaze duration on the comparison pattern relative to the total gaze duration.
- Fixation Duration (FD): Total fixation duration until the task is terminated.
- Re-fixations (RF): Average depth of re-fixation during the task. Re-fixation occurs within a  $2^\circ$  deviation between current and previous fixation. Re-fixation depth is the number of saccades between the current fixation and the previously visited fixation.
- Saccade Orientation (SO): Percentage of "vertical saccade angles." A vertical saccade angle is a saccade angle within the interval  $(90^\circ \pm 7^\circ)$ . A saccade angle is the angle between the current and previous saccade vectors.
- Reaction Time (RT): The time interval between the start of a comparison task and the participant's termination of the task.
- Error Rate (ER): Errors in classification (incorrect details classified as errors).

#### **Collection and Analysis of Cognitive Functions Using Tablet PC**

In the multimodal interactive training "DaheimAktiv," all interactions and events on the tablet PC are recorded, anonymized with a personal code, and then stored in a central database for further data analysis. The results enable a quantitative comparison of the

training games and related performance metrics with the psychological questionnaires to identify suitable correlates.

The MIRA (Mobile Instrumental Review of Attention) software module allows for the automated tracking of the user's eye movements via the webcam. The following modules are designed for data collection and subsequent analysis:

- Component "Trail Making Test": Random patterns are generated in the style of the "Trail Making Test" A and B. The user can engage in a playful manner (as a video game), and the data are recorded.
- Component "Go/Nogo": In the style of a go/nogo test, stimuli are presented sequentially, and the user will interact with corresponding artifacts, which will be available for further analysis.
- Component "TAP-Concentration": Following the "Test of Attentional Performance," concentration is measured during an abstract task. The data can be analyzed via the central database.

### **Lifestyle Factors Using Tablet PC**

The tablet PC will also continuously, yet playfully, collect lifestyle factors to enhance Alzheimer's dementia management (see "Pick-A-Mood," Desmet et al., 2016). These data collection methods are designed to contribute to "serious game" effects that further encourage their use. Users will be rewarded with playful, non-competitively superficial success tableaux, such as a garden where each contribution to data collection grows a flower or tree, creating beautiful botanical displays. This anticipated user engagement can drive further participation. The planned data collection components are:

- "Social Activities": Daily social contacts are recorded by selecting from various buttons, each representing a specific level of social interaction for the day: "no person," "1 person on a chair," "2 people," and so on. → Selection through "Pick-A-Social State."
- Pictorial Representation of Various Mood States: Through "Pick-A-Mood" (see Appendix 2; Desmet et al., 2016).
- Input of Current Weight and Height: With a constant reference from the biographical data section, the current BMI value is graphically and playfully displayed.

- Input of Systolic and Diastolic Blood Pressure Values: If available, with special "reward values" in the serious game.
- Pictorial Representation of Various Daily "Dietary Forms".
- Pictorial Representation of Different "Sleep Patterns".
- Pictorial Representation of Various "Smoking Behaviors".

